#### 4.2.3 Enrollment Visit

For all groups, enrollment is defined as the day of first study injection and is designated Study Day 0. Pregnancy test results for women of reproductive potential must be confirmed as negative on the day of enrollment prior to the study injection. Day 0 evaluations prior to the first injection are the baseline for subsequent safety and immunogenicity assessments. If any evaluation is not performed on Day 0, then the baseline will be the screening evaluation.

#### 4.2.4 Administration of Injections

All Day 0 vaccinations will be administered open-label according to the randomized assignment. Injections of HA DNA will be administered into deltoid muscle in a 1 mL volume using a Biojector 2000® needle-free injection system (Biojector; Bioject Medical Technologies Inc., Portland, OR). The Biojector will be used as directed by the manufacturer. The Biojector uses sterile, single-use syringes for administration of volume up to 1 mL. The study agent is delivered under pressure by a compressed CO2 gas cartridge that is stored inside the Biojector. Neither the material being injected nor injection site skin preparation requires deviation from standard procedures. The CO2 does not come in contact with the injectate and the syringe design prevents any back splatter or contamination of the device by tissue from the subject.

The TIV and ATIV injections will be administered IM into deltoid muscle by needle and syringe, according to directions in the manufacturer's package insert and IB, respectively.

For prime injections in Groups 5 and 6, the two injections administered on Day 0 will be administered in different arms. To assist with data monitoring, HA DNA will be administered in the left arm and the TIV or ATIV (as indicated by the assigned schedule) will be administered in the right arm.

Otherwise, when only a single injection is administered on a given day, it is recommended, but not required, that study injections be administered into the non-dominant arm. When choosing an arm for the injection, clinicians should consider whether there is an arm injury, local skin problem or significant tattoo that precludes administering the injection or will interfere with evaluating the arm after injection.

Following study injection(s), subjects will be observed for a minimum of 30 minutes after injections of the investigational HA DNA vaccine and ATIV injections, and for a minimum of 15 minutes after the licensed TIV injection. Blood pressure and pulse will be taken between 15 and 60 minutes post-injection. The injection site will be inspected for evidence of local reaction. Acute medical care will be provided to subjects for any immediate allergic reactions or other injury resulting from participation in this research study.

**7-Day Diary Card and Follow-up:** Subjects will be given a "Diary Card", to use as a memory aid, on which to record temperature and symptoms daily for 7 days following each injection. The site may use the electronic or written (paper) diary card as a source document or clinician notes obtained by telephone interview as the source of reactogenicity information recorded in the study database.

The solicited signs and symptoms on the diary card will include the parameters: unusually tired/feeling unwell, muscles aches (other than at injection site), headache, chills, nausea, and pain/tenderness at injection site(s). Subjects will also record the day's highest measured

temperature and measurement of largest diameter for redness and swelling at injection site(s). For subjects who receive concurrent administration of DNA and ATIV or TIV pain/tenderness, redness, and swelling will be assessed separately for each injection site.

Subjects will be asked to contact the clinic if they have any concerning signs or symptoms. A clinic visit will be scheduled, if indicated, for the following: rash, urticaria, fever of 38.5°C (Grade 2) or higher lasting greater than 24 hours, or significant impairment in the activities of daily living (ADL). Additionally, other clinical concerns may prompt a study visit based on the judgment of a study clinician.

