In this study, we are evaluating the safety and immunogenicity of same season and sequential season vaccination schedules. The same season regimens (2012/13 prime and boost with a 16 week interval) consist of HA DNA prime with ATIV boost -- or -- HA DNA prime with TIV boost; the active comparator for these regimens will be ATIV or TIV alone because this is the standard for adult influenza vaccination within a single season. The sequential season regimens (2012/13 prime and 2013/14 boost with a 44 week interval) consist of concurrent administration (in different arms) of HA DNA and ATIV prime with ATIV boost -- or -- HA DNA and TIV prime with TIV boost; the active comparator for these regimens will be ATIV followed by ATIV boost or TIV followed by TIV boost, also at a 44 week interval, because this is a vaccination pattern consistent with sequential season vaccinations. Evaluation of these investigational schedules and active comparator schedules will inform development of novel influenza vaccine strategies that may offer improved and cross-protective immunity against antigenically diverse influenza strains.

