#### 3.1 PRIMARY OBJECTIVES:

- To evaluate the safety and tolerability of each vaccination schedule
- To evaluate the safety and tolerability of concurrent administration of the HA DNA vaccine and either ATIV (FLUAD) or TIV (AGRIFLU) administered in different arms on the same day
- To compare the frequency and magnitude of the 2012/13 influenza vaccine strain-specific HAI response at 3 weeks after the ATIV boost in Group 1 to 3 weeks after the ATIV prime in Group 3, as well as to compare the same responses at 3 weeks after the TIV boost in Group 2 to 3 weeks after the TIV prime in Group 4.

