**A. Tables for Clinical Abnormalities**

| Local Reaction to
Injectable Product | Mild
(Grade 1)                       | Moderate
(Grade 2)                                                     | Severe
(Grade 3)                                  | Potentially Life
Threatening
(Grade 4)          |
|-------------------------------------------------|-------------------------------------------------|-----------------------------------------------------------------------------------|--------------------------------------------------------------|----------------------------------------------------------------|
| Pain                                            | Does not interfere with activity                | Repeated use of non-narcotic pain reliever > 24 hours or interferes with activity | Any use of narcotic pain reliever or prevents daily activity | Hospitalization                                                |
| Tenderness                                      | Mild discomfort to touch                        | Discomfort with movement                                                          | Significant discomfort at rest                               | Hospitalization                                                |
|  Erythema/Redness                   | 2.5 – 5 cm                                      | 5.1 – 10 cm                                                                       | > 10 cm                                                      | Necrosis or exfoliative dermatitis requiring medical attention |
|  Induration/Swelling                | 2.5 – 5 cm and does not interfere with activity | 5.1 – 10 cm or interferes with activity                                           | > 10 cm or prevents daily activity                           | Necrosis requiring medical attention                           |
|                                                 |                                                 |                                                                                   |                                                              |                                                                |

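### Section 4.2.4 sets one arm rule for the Day 0 TIV/ATIV injection in Groups 5-6 and another in their randomised comparators, Groups 3-4, so the descriptive comparison of local pain and swelling may partly reflect arm dominance

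*Protocol*

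**What the plan says.** Protocol section 4.2.4 has two arm rules. For the Day 0 prime in Groups 5 and 6 the sides are fixed. HA DNA goes on the left, a choice the protocol explains by data monitoring. For the other product the rule is that "the TIV or ATIV (as indicated by the assigned schedule) will be administered in the right arm". For any day with a single injection, "it is recommended, but not required, that study injections be administered into the non-dominant arm"; the clinician is also to consider an injury, skin problem or tattoo on the arm. This second rule covers the Day 0 TIV or ATIV injection in Groups 3 and 4, both injections in Groups 1 and 2, and the boost in Groups 3-6.

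Groups 3 and 4 are the controls for Groups 5 and 6. On the sequential-season co-administration regimens, section 1 states that "the active comparator for these regimens will be ATIV followed by ATIV boost or TIV followed by TIV boost". Sections 6.4 and 6.5.6 randomise the last 220 subjects equally to Groups 3-6.

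Safety and tolerability of giving HA DNA with TIV or ATIV in different arms on the same day is a primary objective in its own right (section 3.1). For subjects with two injections, "pain/tenderness, redness, and swelling will be assessed separately for each injection site" (section 4.2.4). Section 6.5.3 tabulates each sign or symptom at the subject's maximum severity. In Appendix IV, pain reaches Grade 2 or Grade 3 through its effect on activity, and swelling reaches Grade 2 at "5.1 – 10 cm or interferes with activity". Redness is graded by diameter alone up to Grade 3.

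**The concern.** Group 5 against 3 and Group 6 against 4 are the randomised contrasts that isolate the effect of adding HA DNA to TIV or ATIV on Day 0. If the TIV/ATIV injection also goes to a different arm in the two members of each pair, adding DNA and changing arm are mixed. Because the arm rule is assigned with the group, randomisation and a larger sample leave the difference in place.

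A right-handed subject in Group 5 or 6 gets TIV or ATIV in the working arm. A right-handed subject in Group 3 or 4 whose clinician follows the recommendation gets it in the other arm. Soreness that interferes with activity in the first case may not in the second. An excess of Grade 2 pain at the TIV/ATIV site in Groups 5-6 could then be read as an effect of co-administration. Section 4.3 says these products have not been given on the same day before, so readers will look to this trial for that answer.

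**Working it through.** The protocol states no figure for arm use, so there is none to reproduce. The check sizes the imbalance and then asks what it could do to a tabulated rate.

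**Inputs**
- TIV/ATIV arm in Groups 5-6: right, fixed (section 4.2.4).
- TIV/ATIV arm in Groups 3-4 at prime: non-dominant, recommended only (section 4.2.4).
- Group size: 55 (section 6.4.1).
- r, the share of right-handed subjects: not in the protocol; assumed 0.80 to 0.95.
- c, the share of Groups 3-4 injected in the non-dominant arm: not in the protocol; assumed 0.50 (dominance ignored) to 1.00 (always followed).
- e, the rise in the rate of a graded local reaction caused by using the dominant arm: not in the protocol; assumed 5, 10 or 15 percentage points.

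**Step 1: imbalance in arm used.** The right arm is the dominant arm only for right-handed subjects, so the dominant-arm share is r in Groups 5-6 and 1 - c in Groups 3-4.

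Imbalance = r - (1 - c)

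| r | c = 0.50 | c = 0.75 | c = 1.00 |
|---|---|---|---|
| 0.80 | 0.30 | 0.55 | 0.80 |
| 0.90 | 0.40 | 0.65 | 0.90 |
| 0.95 | 0.45 | 0.70 | 0.95 |

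The range is 30 to 95 percentage points.

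**Step 2: apparent group difference from arm alone.** Shift = e x imbalance.
- e = 5 points: 5 x 0.30 = 1.5 to 5 x 0.95 = 4.75 points.
- e = 10 points: 3.0 to 9.5 points.
- e = 15 points: 4.5 to 14.25 points.

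In a group of 55 the extremes are 0.015 x 55 = 0.8 subjects and 0.1425 x 55 = 7.8 subjects.

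**Step 3: set against the study's resolution.** Table 6-3 gives 46% to 68% power at 55 per group for a 20-point difference, over rate pairs from 0.4 vs 0.6 to 0.7 vs 0.9. Exact Fisher calculations return 46.5%, 49.1%, 56.0% and 68.2% for the four 20-point pairs, in line with the table. That table concerns seroconversion, but the arithmetic holds for any two proportions. A shift of the size in Step 2 would seldom reach significance. It could still move a descriptive severity table by several subjects.

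**The case against.** The strongest reply is that the link from arm to grade is assumed. Nothing in the protocol shows that a dominant-arm injection changes the rate or grade of local reactions, so Step 1 measures an imbalance in arm used and not a bias in a safety result. This stands. The grading criteria make the mechanism plausible but give no size.

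Second, no comparison of local reactions between these groups is specified. The objective is to evaluate, section 6.5.3 plans tabulation, and section 6.4 disclaims a formal superiority or non-inferiority hypothesis. This also stands, but the comparator role in section 1 invites the side-by-side reading, and an arm imbalance distorts a descriptive contrast as it would a test.

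Third, the affected endpoint is narrow. Section 6.3.1 defines the primary endpoint as occurrence, while the mechanism acts mainly on grade. Redness up to Grade 3 is graded by size, and the measured diameter is also kept as a continuous variable. What remains is pain, and swelling graded by function.

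A reader might infer more than the documents support:
- *Near-complete confounding in all 110 Group 5-6 subjects.* This needs full adherence to a non-binding recommendation and sits at the top of the range. For left-handed subjects the right arm is the non-dominant one.
- *The DNA-site versus TIV/ATIV-site contrast within a subject is spoiled by side.* It is not a stated objective. The sites already differ in product, in device (Biojector against needle and syringe) and in volume (1 mL against 0.5 mL), so a common arm rule would not rescue it.
- *The boost is affected too.* All of Groups 3-6 follow the same recommendation at the boost, so no difference in rule arises there.
- *Arm and handedness go unrecorded.* The protocol does not itemise its case report forms, so its silence does not show this.

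**Conclusion.** The point holds as a limited, avoidable asymmetry. The same product on the same day follows a fixed right-arm rule in Groups 5-6 and a recommended non-dominant-arm rule in their randomised comparators. Under the assumed ranges for handedness and adherence, dominant-arm use differs by about 30 to 95 percentage points. If arm dominance shifts a graded reaction by 5 to 15 points, which is also an assumption, the apparent difference from arm choice alone is about 1.5 to 14 points. If adherence in Groups 3-4 were below 50%, the imbalance would be smaller.

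The consequence is confined to the descriptive Group 5 versus 3 and Group 6 versus 4 comparisons of TIV/ATIV-site pain and functionally graded swelling after the prime. Immunogenicity, systemic reactions, SAEs and size-graded redness are not shown to be affected. It is worth correcting because it touches a primary objective and costs little.

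**What to change.** Reconcile the two arm rules in section 4.2.4 so that one convention governs the Day 0 TIV/ATIV injection in all of Groups 3-6, keeping the existing exceptions for injury, skin problem and tattoo. Either existing convention serves the comparison if all four groups share it; the choice is the sponsor's. Confirm that arm used and handedness are captured with each vaccination, so that site-specific local reactions in Group 5 versus 3 and Group 6 versus 4 can be described on like arms. If the rules cannot be aligned, those two fields alone would still allow a description by arm dominance.

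The cost is one sentence and two data fields, plus one of two losses. Either Groups 3-4 give up the non-dominant-arm recommendation at the prime, or Groups 5-6 give up the fixed left/right mapping that the protocol adopted for data monitoring.

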#### **4.2.5 Blood Sample Collection**

At intervals throughout the study, blood will be drawn for safety and immunologic assays. Blood will be drawn from the arm veins of subjects by standard phlebotomy procedures.

#### **4.2.6 Concomitant Medications and Procedures**

Current concomitant medications are recorded in the study database at enrollment. Concomitant medications will be updated in the study database if there is an occurrence of an adverse event that requires expedited reporting. Treatment for influenza with antiviral drugs will be recorded on an Influenza Endpoint Case Report Form. Sites should work with study subjects with regard to the timing of FDA-approved vaccines such that, when possible, they should be scheduled at least 14 days before or at least 28 days after a study vaccination. Receipt of a licensed vaccine at any time is not a protocol violation. Vaccinations received during study participation will be recorded in the study database. Otherwise, a record of concomitant medication changes throughout the study will not be recorded in the study database.

### **4.3 CRITERIA FOR COMPLETING RANDOMIZATION INTO GROUPS 5 AND 6**

Group 5 and Group 6 have a prime injection plan that includes an injection in each arm with products that have not been previously co-administered on the same day. Therefore, once concurrent randomizations into Groups 3, 4, 5 and 6 begin, no more than 20 subjects per week may be enrolled in the first two weeks. This rate of enrollment will limit the number of subjects randomized to receive the prime injections in Group 5 and Group 6 initially. The initial controlled rate of enrollment will allow the Protocol Safety Review Team (see Section 8.8) to conduct at least two weekly interim safety data review of cumulative safety data before larger numbers of subjects are randomized to Groups 5 and 6. Weekly, the PSRT will advise whether enrollment to complete all Groups may proceed or if a safety concern is identified, whether enrollment should be paused until consultation with the FDA is completed. After the first two weeks of randomization to Groups 3-6, if no safety concerns are identified, the rate of enrollment may proceed at higher numbers per week until completion of the target accrual.

### **4.4 CRITERIA FOR DISCONTINUING STUDY INJECTIONS OR PROTOCOL PARTICIPATION**

In general, subjects who receive the Day 0 study injection will continue to be followed, whenever possible, as indicated on the schedule of evaluations.

#### **4.4.1 Discontinuation of Study Injections**

For those who begin a schedule, discontinuation of the injection schedule may occur for the following reasons:

1. Subject declines to receive the second study injection.

2. Circumstances have arisen that constitute a contraindication to administering the vaccine as indicated by the package insert for TIV or the Investigators Brochure for ATIV or as based on the clinical judgment of the IoR or Protocol Chair.
3. The Site IoR assesses that it is not in the best interest of the subject to continue on the vaccination schedule.

Pregnancy is not a contraindication to the licensed TIV, but research blood draws will be adjusted as indicated in **Appendix III**.

ATIV is not licensed in the U.S.; therefore, administration of ATIV to a pregnant subject is not permitted in this protocol. If the ATIV boost is not given due to pregnancy, the subsequent research blood draws should be discontinued. The TIV injection can be offered by the site to subjects who became pregnant on the study as a standard of care.

#### 4.4.2 Discontinuation from Protocol Participation

A subject may be discontinued from protocol participation for the following reasons:

1. Subject decides to discontinue participation.
2. Subject develops a medical condition that is a contraindication to continuing study participation.
3. The Sponsor or regulatory authority stops the protocol.
4. The Site Investigator of Record (IoR) assesses that it is not in the best interest of the subject to continue participation in the study or that the subject's compliance with the study is not sufficient.

#### **4.5 CRITERIA FOR PAUSING THE STUDY**

The Protocol Chair and UNI-CPSC Medical Monitor will closely monitor and analyze study data as they become available. The VRC Medical Officer will provide an independent review of adverse events on a regular basis. The administration of study injections and new enrollments will be paused if one (or more) subject experiences a Grade 4 or Grade 5 adverse event that is assessed as related to a study vaccine.

The study injections and enrollments would resume only if review of the adverse event(s) that caused the pause resulted in a recommendation to permit further study injections and study enrollments. The Protocol Safety Review Team (PSRT) will conduct the review and make a decision to resume or close the study. Changes in study status will be communicated to the study sites promptly by the UNI-CPSC.

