### 5.1.2 Adverse Event Reporting in the Study Database

The following guidelines will be used to determine whether or not an adverse event is recorded in the study database.

Each adverse event will be graded according to the table for grading severity of adverse events (see **Appendix IV**).

Solicited adverse events will be recorded in the study database separately with data collection for 7 days after both the first vaccination and the second injection as detailed in Section 4.2.4; without the collection of attribution assessments. All unsolicited AEs will be recorded in the study database from receipt of first study injection through 28 days after each study injection. At other time periods between injections and after the second injection, only SAEs (as detailed in **Section 5.2**), new chronic medical conditions, and influenza or influenza-like illness will be recorded through the last study visit. However, cases of influenza or influenza-like illness will be recorded on an influenza endpoints form rather than on an adverse events form.

Any adverse events associated with licensed TIV that meet the criteria for reporting under the Vaccine Adverse Events Reporting System (VAERS) system, are the responsibility of the IoR to report in accordance with the guidance on reportable events available at the website <http://vaers.hhs.gov/professionals/index>. Refer to the brochure with description and guidance to the VAERS system, which is co-sponsored by the Centers for Disease Control and Prevention (CDC) and the Food and Drug Administration (FDA): [http://vaers.hhs.gov/resources/VAERS\\_Brochure.pdf](http://vaers.hhs.gov/resources/VAERS_Brochure.pdf).

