## 5.2 **SERIOUS ADVERSE EVENTS**

### 5.2.1 Serious Adverse Event Definition

The term “Serious Adverse Event” (SAE) is defined in the 21 CFR 312.32 in terms of the following outcomes: Death, a life-threatening adverse event, inpatient hospitalization or prolongation of existing hospitalization, a persistent or significant incapacity or substantial disruption of the ability to conduct normal life functions, or a congenital anomaly/birth defect. Important medical events that may not result in death, be life-threatening, or require hospitalization may be considered serious when, based upon appropriate medical judgment, they may jeopardize the patient or subject and may require medical or surgical intervention to prevent one of the outcomes listed in this definition. Examples of such medical events include allergic bronchospasm requiring intensive treatment in an emergency room or at home, blood dyscrasias or convulsions that do not result in inpatient hospitalization, or the development of drug dependency or drug abuse.”

An SAE will be considered "life-threatening" if, in the view of either the investigator or sponsor, its occurrence places the patient or subject at immediate risk of death. It does not include an adverse event or suspected adverse reaction that, had it occurred in a more severe form, might have caused death.

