#### 6.5.5 Interim Analyses

**Safety Reviews:** The protocol safety review team will review safety data routinely throughout the study. The study will utilize both electronic database features and reviews by designated safety review personnel to identify in a timely manner if any of the safety pause rules of the study are met.

**Immunogenicity Review:** The analyses of immunogenicity may be performed when the HAI assays at 3 weeks after the ATIV or TIV injections in Groups 1 and 2 and the HAI assays at 3 weeks after the prime ATIV or TIV injections in Groups 3-6 have been completed for the study, which may occur prior to completion of safety follow-up visits or collection of data for secondary and exploratory immunogenicity endpoints. Such an analysis would constitute the final analysis for the primary immunogenicity endpoint, so sample size adjustments are not required. Reports providing results by study group may be provided to VRC solely for the purpose of informing decisions related to future trials in a timely manner. The results should in no way influence the conduct of the VRC 703 trial in terms of early termination or later safety or immunogenicity endpoint assessments. Analyses secondary and exploratory immunogenicity assays may also be performed as data are available.

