### **Grading the Severity of Adverse Events:**

The FDA Guidance for Industry (September 2007): “Toxicity Grading Scale for Healthy Adult and Adolescent Volunteers Enrolled in Preventive Vaccine Clinical Trials” is the basis for the severity grading of adverse events in this protocol. Several modifications were made to the table as follows:

- “Emergency room visit” is not automatically considered a life-threatening event; these words have been removed from any “grade 4” definition where they appear in the table copied from the guidance document.
- Any laboratory value shown as a “graded” value in the table that is within the institutional normal range will not be severity graded or recorded as an adverse event.
- Severity grading for hemoglobin decrease on the basis of the magnitude of decrease from baseline is not applicable at the grade 1 level; only absolute hemoglobin will be used to define grade 1 decrease. Increases in hemoglobin are AEs only for values above the upper limit of normal and are graded by the systemic illness clinical criteria.
- Severity grading definition for Grade 4 local reaction to injectable product (Erythema/Redness and Induration/Swelling) included added text “requiring medical attention”.
- 1 X ULN was removed from the definition for PT increase.
- Severity grading definition for hypotension includes added clarifications such that an asymptomatic low blood pressure reading is not an adverse event.

When not otherwise specified in the table, the following guidance will be used to assign a severity grade:

**Grade 1 (Mild):** No effect on activities of daily living

**Grade 2 (Moderate):** Some interference with activity not requiring medical intervention

**Grade 3 (Severe):** Prevents daily activity and requires medical intervention

**Grade 4 (Life-threatening):** Hospitalization; immediate medical intervention or therapy required to prevent death.

**Grade 5 (Death):** Death is assigned a Grade 5 severity.

Only the single adverse event that is assessed as the primary cause of death should be assigned “grade 5” severity.

**Toxicity Grading Scale for Healthy Adult and Adolescent Volunteers Enrolled in  
Preventive Vaccine Clinical Trials  
FDA Guidance - September 2007**

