| Fatigue                   | No interference with activity                            | Some interference with activity                                                          | Significant; prevents daily activity                                             | Hospitalization                                       |
| Myalgia                   | No interference with activity                            | Some interference with activity                                                          | Significant; prevents daily activity                                             | Hospitalization                                       |

| Systemic Illness                                                            | Mild
(Grade 1)     | Moderate
(Grade 2)                                      | Severe
(Grade 3)                               | Potentially Life
Threatening
(Grade 4) |
|------------------------------------------------------------------------------------|-------------------------------|--------------------------------------------------------------------|-----------------------------------------------------------|-------------------------------------------------------|
| Illness or clinical adverse event (as defined according to applicable regulations) | No interference with activity | Some interference with activity not requiring medical intervention | Prevents daily activity and requires medical intervention | Hospitalization                                       |

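### Appendix IV defines Grade 4 in two ways, so a related life-threatening reaction treated without admission can be graded 3 and miss the mandatory pause in Section 4.5

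*Protocol*

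**What the plan says.** Section 4.5 has one mandatory trigger: injections and new enrollments are "paused if one (or more) subject experiences a Grade 4 or Grade 5 adverse event that is assessed as related to a study vaccine". The Protocol Safety Review Team (PSRT) then reviews the event and decides whether the study resumes or closes.

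Section 5.1.2 says how the grade is set: "Each adverse event will be graded according to the table for grading severity of adverse events", referring to Appendix IV.

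Appendix IV holds two sets of grade definitions that bear on a clinical event without its own row:

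- Table A, Systemic Illness, has a single row, "Illness or clinical adverse event (as defined according to applicable regulations"). Its Grade 4 cell contains one word, hospitalization.
- The general guidance ahead of the tables defines Grade 4 as "Hospitalization; immediate medical intervention or therapy required to prevent death". It is introduced as a fallback: "When not otherwise specified in the table, the following guidance will be used to assign a severity grade".

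Section 5.2.1 calls a serious event life-threatening when "its occurrence places the patient or subject at immediate risk of death". Admission to hospital is not part of that definition.

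Section 6.5.5 relies on database features and designated safety reviewers "to identify in a timely manner if any of the safety pause rules of the study are met".

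**The concern.** The pause rule is only as reliable as the grade that feeds it. If one reaction can properly be recorded as Grade 3 or as Grade 4, depending on which part of Appendix IV the investigator uses, the one-event rule does not have a fixed meaning.

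The case is foreseeable from the protocol. Section 8.5.3 lists acute, possibly life-threatening allergic reactions among the risks of the inactivated vaccine, and Section 8.5.4 carries those risks over to the adjuvanted product. Section 4.2.4 plans for on-site treatment: "Acute medical care will be provided to subjects for any immediate allergic reactions". Section 5.2.1 gives intensive emergency-room or home treatment of allergic bronchospasm as an example of an event that can be serious without the outcomes listed there. A severe reaction treated promptly and sent home is therefore a realistic case. What is at stake is whether dosing stops before the event is reviewed or continues while it is reviewed.

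**Working it through.** The protocol gives no figure to reproduce on this point. The check sets the texts side by side and runs one test case through them.

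**1. The two definitions compared**

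| Grade | Systemic Illness row (Table A) against general guidance |
|---|---|
| 1 | Trivial difference in wording |
| 2 | Same wording |
| 3 | Same wording: daily activity prevented and medical intervention needed |
| 4 | Row: hospitalization only. Guidance: hospitalization, and also immediate treatment needed to prevent death |

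The only difference of substance is at Grade 4, where the pause begins.

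**2. Which text takes precedence**

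The guidance applies only where the table does not specify a grade. The row is worded to cover any illness or clinical adverse event, so on a literal reading the table always specifies one and the row governs. Appendix IV itself uses the row as a default: its list of modifications sends hemoglobin increases, which have no row of their own, to the systemic illness criteria.

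**3. Test case**

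Take an anaphylactic reaction judged related to vaccine, which needs immediate treatment to prevent death, is managed in the clinic or emergency room, and resolves without admission.

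- By the row: medical intervention but no hospitalization, so Grade 3. Section 4.5 is not met.
- By the guidance, or by the column heading, which calls Grade 4 potentially life-threatening: Grade 4. Section 4.5 is met by this one subject.

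An emergency room visit does not settle the matter. Appendix IV states that it was deliberately removed from the Grade 4 definitions. That is a legitimate choice, but it leaves hospitalization as the row's only criterion. The hypotension row works the same way: symptomatic systolic pressure below 80 mm Hg needing IV fluids is Grade 3, and Grade 4 requires hospitalization for hypotensive shock.

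**4. Exposure under the rule** (from Table 4-1, 55 subjects per group)

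- Vaccination visits: 330 × 2 = 660.
- HA DNA injections (Groups 1, 2, 5, 6): 4 × 55 = 220.
- ATIV injections (Groups 1, 3, 5): 55 + 110 + 110 = 275.
- TIV injections (Groups 2, 4, 6): 55 + 110 + 110 = 275.
- Total: 220 + 275 + 275 = 770.

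These are counts of opportunities, not a measure of risk.

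**The case against.** The strongest reply is that the harmful reading goes against the appendix's own labels. Both the guidance and the column heading present Grade 4 as the life-threatening grade, so an investigator would have to file a reaction judged life-threatening under severe. If the catch-all row specifies every clinical event, the guidance has almost nothing clinical left to govern; a reading that gives both texts effect would send anaphylaxis to the guidance, and so to Grade 4. The note on emergency room visits removes only an automatic upgrade, which suggests the sponsor still meant true life threat to be Grade 4. The table is openly based on the regulator's scale.

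Central review also lies on the path. Serious events are reported within 24 hours, and database entry sends automatic e-mail to the Medical Monitor and Medical Officer (Section 5.2.2). Section 4.5 provides independent review of adverse events, and the PSRT oversees safety in real time (Section 5.4).

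Much of this stands. Many investigators would choose Grade 4, and the event would not go unseen. It does not remove the conflict. The hemoglobin instruction shows that the row does serve as a default for events without their own row, so the literal reading cannot be dismissed. Reporting is mandatory, but a decision to stop injections after a Grade 3 entry would be a matter of judgment. Section 4.5 is built the other way round: stop first, then review.

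**Conclusion.** The concern holds, as an ambiguity and not as a certain miss. A related life-threatening reaction treated without admission can be graded 3 on a faithful reading of Appendix IV, and the mandatory pause would then not be triggered. Two sites could grade the same event differently.

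The size cannot be given as a probability, because the protocol gives no rate for such reactions. They should be rare: Section 1.4.2 reports no vaccine-related serious adverse events in the HA DNA trials to date. The consequence of one such event is nevertheless all or nothing, because the threshold is one. The rule also covers Groups 5 and 6, whose same-day products had not been given together before (Section 4.3).

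The conclusion assumes that the semicolon in the guidance's Grade 4 definition means or, and that the reaction falls under no more specific row. It does not touch the design, endpoints, sample size or analysis. It should be corrected because it concerns the only automatic safety stop in the protocol.

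**What to change.** Change the Grade 4 cell of the Systemic Illness row so that it carries both limbs of the general guidance: hospitalization, or immediate medical treatment needed to prevent death. The row, the guidance and the column heading then agree.

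Preferably, also add one sentence to Section 4.5: a related serious event that is life-threatening under Section 5.2.1 triggers the pause whatever its table grade. This also covers events graded on a specific row, such as hypotension, which the cell change would not reach.

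The cost is one table cell and one sentence. In operation, the downside is an occasional additional short pause, resolved through the existing PSRT review.
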